#### Control group (CG)

The CG receives no study-specific additional therapy during the intervention phase but is free to undergo all established psychotherapeutic and psychiatric treatment options and therefor represent treatment as usual in the German Health Care System. Participants allocated to the CG are given city vouchers (that can be redeemed in numerous regional shops and locations) or free passes to the local bouldering hall after completing measurement times t1 and t2. If interested, they are also offered preferential admission to the outpatient BPT group at Erlangen University Hospital after t1.

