#### Other variables

During enrollment, interested people are participating in a computer-assisted diagnostic video *screening interview* to assess the inclusion and exclusion criteria before being told whether they can participate in the study. The interviewer assesses the following data: *age*, *sex*, *height*, and *weight* to determine *body mass index* (BMI), *current outpatient group therapy*, *current psycho-pharmacotherapeutic treatment*, *physical limitations*, *psychiatric comorbidities*, *preferences concerning future group allocation* (BPT, MMT, CG), and *depressive symptoms*. The presence of a current depressive episode is measured with a structured interview based on the DSM-V diagnostic criteria [53]. It includes the assessment of the participants’ current depression as well as past episodes and age of onset.

At baseline, further sociodemographic data, such as *family status*, *level of education*, and *current occupation*, are being assessed via a questionnaire. In a video interview, the following additional data are being collected: *current and past psychotherapeutic treatment* (inpatient and outpatient), *experiences with mindfulness and meditation*, and *participation in sports for the treatment of depression*.

*Changes concerning current psycho-pharmacotherapeutic and psychotherapeutic treatment* are being assessed with a video interview shortly after as well as 12 months after the intervention.

*Critical events*, such as injuries, accidents, mental crises, or hospitalization, as well as their intensity (mild, medium, severe), during the intervention period and during the year following the intervention are being assessed shortly after and 12 months after the intervention. The intensity of these events is judged on the basis of the extent of the impact on the participant’s life and the resulting need for treatment.

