#### Quantitative measurements

The primary hypothesis will be tested via mixed model ANOVAs with which potential interactions between time and group can be detected. To test the first and second hypotheses, a mixed model ANOVA with the between-subjects factor group and the within-subjects factor time as well as the group × time interaction will be calculated. Additionally, multiple regression analyses will be calculated to control for the effects of possible confounding variables (e.g., demographics, additional therapeutic treatments, such as antidepressant medication and psychotherapy).

Secondary outcome variables will be tested in an exploratory fashion with mixed model ANOVAs.

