## Discussion

In this article, we presented the design for a randomized controlled trial to test the efficacy of two short-term group therapies for outpatients with depression using a mixed methods approach. In addition to quantitative data collection, qualitative data on factors of influence for each intervention will be analyzed. The study could offer important insight into the effectiveness and potential factors of influence of short-term group therapies that have up to now been less well studied than individual therapies [13].

The group therapies that are being investigated in the present study are, first, BPT, whose effectiveness has already been investigated in two RCTs [23, 25] and, second, a newly developed cognitive-based group therapy with mental models.

Both interventions consist of innovative new elements with an effective therapeutic background: BPT includes contents of physical activity and body experience, MMT the element of mental models with a long-term influence derived from research on decision making [30, 31]. As a significant number of patients still do not profit from existing psychotherapies [10], it seems sensible to develop different types of therapies and identify possible factors of influence in order to be able to personalize the therapeutic technique to enhance the benefits of this technique for all at a later stage of development.

During and after the intervention period, participants are free to begin or continue other therapeutic treatments offered by the German health care system without suffering any disadvantages. Previous ongoing treatment plans will not be changed by their participation in this study. Therapeutic treatment outside of the study will be assessed in the video interviews.

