The strengths of the present study are the randomization, the mixed methods approach, the naturalistic design with very few exclusion criteria, and the longitudinal character of the study with a long follow-up period of 1 year after the end of treatment. The use of manualized treatments in a naturalistic setting will contribute to the high internal and external validity of the study. The inclusion and exclusion criteria are being assessed via diagnostic screening interviews in contrast to self-report assessments. Additionally, the severity of depressive symptomatology as the primary outcome is being collected by blinded interviewers, and the interrater reliability is being assessed. A methodological limitation might be a possible selection bias due to people choosing to participate because they are interested in the therapies. Therefore, group preference is being taken into account during randomization, and it will be possible to compare subgroups with respect to their group preference. Also, the selection of a specific therapy on the basis of interest in the intervention is naturalistic and will hence contribute to higher external validity. Another limitation is the fact that the psychotherapeutic interventions themselves cannot be blinded. Furthermore, the clinical heterogeneity of the sample could lead to a reduction in effect sizes but would also strengthen external validity. As participants are free to continue with or begin other individual treatments during the study, possible confounding effects due to simultaneous interventions cannot be ruled out. However, ongoing and new treatments as well as changes in treatment plans during the study will be assessed at all measurement points, and the data will be considered in the analyses.

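### The supplementary regressions treat outside therapy as a confounder without limiting it to baseline status, so their adjusted group effect may not be the effect versus usual care and is liable to bias

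*Protocol article*

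**What the plan says.** Under *Quantitative measurements*, the protocol article tests both hypotheses with a mixed model ANOVA containing group, time and their interaction. It then adds multiple regressions to control for "possible confounding variables (e.g., demographics, additional therapeutic treatments, such as antidepressant medication and psychotherapy". No time point is attached to the treatments.

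Other sections bear on the timing:

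- *Discussion*, limitations: because patients may continue or start other treatment during the study, the article says confounding cannot be excluded. Its answer is that "ongoing and new treatments as well as changes in treatment plans during the study will be assessed at all measurement points"; it adds that the analyses will take this information into account.
- *Discussion*, earlier: during and after the intervention period, "participants are free to begin or continue other therapeutic treatments offered by the German health care system".
- *Other variables*: changes in medication and psychotherapy "are being assessed with a video interview shortly after as well as 12 months after the intervention". Current medication is recorded at screening, and current and past psychotherapy at baseline.
- *Control group (CG)*: this arm receives no study therapy and "is free to undergo all established psychotherapeutic and psychiatric treatment options". If interested, "they are also offered preferential admission to the outpatient BPT group at Erlangen University Hospital after t1".

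*Data analysis* makes intention to treat the primary strategy.

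**The concern.** A confounder of a randomised comparison would have to influence allocation. Treatment begun after allocation cannot. It can be influenced by the arm (a control patient without study therapy may look elsewhere) and by how the patient is doing (someone who worsens is more likely to start something). Conditioning on it can remove part of the effect of allocation, open a spurious path between arm and outcome through unmeasured clinical course, or do both.

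There is also a question of meaning. The stated aim is a comparison with treatment as usual, and uptake of ordinary care is what treatment as usual consists of. Holding uptake fixed asks about a different comparator.

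At stake is the reading of the supplementary estimate. If it differs from the ANOVA result, the difference could be put down to confounding removed when the adjustment itself produced it.

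**Working it through.** **Step 1: which treatments are meant?** The regression sentence alone fits either baseline or later treatment. The limitations paragraph in the *Discussion* uses the language of confounding for treatments patients continue or begin during the study, and commits to considering the data on new and changed treatments. *Other variables* shows those data come from t1 and t2, after randomisation. Read together, the sections point to post-randomisation treatment as at least part of what is to be controlled. This is an inference from several sections, not a statement in the regression sentence.

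**Step 2: can uptake depend on arm?** At t1 this is plausible but not documented: all arms may start other care, and only the controls have no study therapy. At t2 the link is clearer, because only the controls are offered priority admission to BPT, after t1 and before the 12-month assessment.

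**Step 3: the plan's own figure.** *Sample size estimation* gives f = 0.295 and N = 114. With λ = f²·N = 0.087025 × 114 = 9.92 and 2 and 111 degrees of freedom at α = .05, power is 0.801, so N = 114 is reproduced. The present point does not affect it. For two groups d = 2f = 0.59, which serves below as an illustrative effect size.

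**Step 4: illustration of the mechanism.** All inputs except 0.59 and the correlation of .50 are assumed. There are two arms, with A = 1 for intervention, and 400,000 simulated patients per setting. Baseline y0, clinical course U (unmeasured) and error e are standard normal.

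- Later treatment: M = 1 if e + a·A + u·U + 0.3·y0 > 0.8
- Outcome: Y = 0.5·y0 − 0.59·A + b·M + 0.6·U + residual, residual variance 1 − 0.25 − 0.36 = 0.39

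Total is the coefficient of A in the regression of Y on A and y0. Adjusted is the same with M added. Negative values favour the intervention.

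| a | u | b | Uptake CG / intervention | Total | Adjusted |
|---|---|---|---|---|---|
| 0 | 1.0 | −0.4 | 29.2% / 29.1% | −0.591 | −0.591 |
| −0.6 | 0 | 0 | 22.3% / 9.0% | −0.589 | −0.589 |
| −0.3 | 0.5 | 0 | 24.5% / 17.1% | −0.587 | −0.552 |
| −0.6 | 1.0 | 0 | 28.9% / 16.6% | −0.588 | −0.499 |
| −1.0 | 1.0 | 0 | 28.9% / 10.7% | −0.593 | −0.458 |
| −1.0 | 0 | −0.4 | 22.2% / 4.2% | −0.516 | −0.588 |
| −0.3 | 0.5 | −0.4 | 24.7% / 17.1% | −0.560 | −0.556 |
| −1.0 | 1.0 | −0.4 | 29.0% / 10.7% | −0.521 | −0.459 |

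Reading the rows:

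- Uptake unrelated to arm (row 1): no shift. Uptake that depends on arm but has no effect and shares no unmeasured cause with the outcome (row 2): no shift.
- Inert treatment, uptake driven by arm and course (rows 3 to 5): the effect shrinks by 0.035/0.587 = 6%, 0.089/0.588 = 15% and 0.135/0.593 = 23%, wholly through the adjustment.
- Active treatment, uptake driven by arm only (row 6): the estimate grows by 0.072/0.516 = 14%. It recovers the direct effect, which is a different question from the effect versus usual care.
- Active treatment with both drivers: the two coefficients can nearly agree because the shifts cancel (row 7), or the adjusted one can match neither the total effect nor the direct effect of −0.59 (row 8).

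**The case against.** The strongest reply is that the regression sentence gives no timing and only examples. Baseline medication and psychotherapy are collected and are legitimate covariates, so the sentence may mean nothing more. Considering the data could mean tabulating them, and an article may leave the covariate list to a fuller plan. This stands in part: it is why the point rests on the *Discussion* and *Other variables* as well. It does not dispose of the point, because the article itself applies the word confounding to treatment begun during the study.

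Second, the regressions are additional. A reader might infer that the primary result is biased. The documents do not support that: the hypotheses are tested by an ANOVA with group, time and their interaction only, under intention to treat.

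Third, a reader might infer that the adjusted effect will be presented as the confounder-free one. No section says so, and the *Discussion* lists concurrent treatment as a limitation.

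Fourth, the shifts are modest against sampling error. With 40 per arm and a correlation of .50, the standard error of a baseline-adjusted difference is about √(2/40 × 0.75) = 0.19 SD, so even the largest shift above, 0.135, is about 0.7 of a standard error. That is fair on size. It also means the trial's data could not show whether a gap between the two analyses was bias or chance.

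Finally, an inert added treatment sits poorly with the article's own *Background*, which calls psychotherapy effective. That is why the active-treatment rows are included, and they show that the direction is not fixed.

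**Conclusion.** The point holds as a correction to the supplementary regressions. They name outside treatment as a confounder, set no baseline limit, and the surrounding text indicates that post-randomisation treatment is included. If so, the adjusted group effect would not estimate the effect versus usual care.

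Bias in that effect is conditional. It requires uptake to depend on arm, and in addition either an effect of the added treatment or an unmeasured cause shared with the outcome. The design makes dependence on arm plausible at t1 and more clearly so at t2. No uptake rates are given, so neither size nor direction can be stated; the range above, from no shift to 23% smaller or 14% larger, illustrates assumed inputs and is not a forecast. Demographics and baseline treatment status remain proper covariates.

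**What to change.** 1. State that covariates in these regressions are limited to variables measured before randomisation: demographics, baseline medication and psychotherapy, baseline MADRS and treatment preference. The article places t0 before therapy begins, so the wording should make clear that the t0 values used describe status before allocation.
2. Report treatment started or changed after t0 descriptively, by arm and separately for t1 and t2, including BPT taken up by controls after t1.
3. State that any model adjusting for post-randomisation treatment is not to be read as a confounder-adjusted treatment effect. Align the *Discussion* sentence that "changes in treatment plans during the study will be assessed at all measurement points, and the data will be considered in the analyses" with this.

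The cost is wording only, since all the variables are already collected. The price is that there will be no estimate of the effect net of added treatment, which this design could give only under strong assumptions that its data cannot test.

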#### Qualitative data

The qualitative data on the factors of influence of the IGs will be analyzed using the software *MAXQDA*. Qualitative content analysis will be performed in accordance with Mayring’s specifications and the principles of thematic content analysis [87, 88]. First, a literature-based coding system encompassing the known factors of influence of psychotherapy will be developed [77]. This approach will be informed from the bottom-up development of codes from the interviews. The coding system will be developed by at least two trained researchers and its aptness verified in an iterative process according to the material. Around 10% of the interviews in each group will be used to calculate the interobserver agreement.

## Discussion

In this article, we presented the design for a randomized controlled trial to test the efficacy of two short-term group therapies for outpatients with depression using a mixed methods approach. In addition to quantitative data collection, qualitative data on factors of influence for each intervention will be analyzed. The study could offer important insight into the effectiveness and potential factors of influence of short-term group therapies that have up to now been less well studied than individual therapies [13].

The group therapies that are being investigated in the present study are, first, BPT, whose effectiveness has already been investigated in two RCTs [23, 25] and, second, a newly developed cognitive-based group therapy with mental models.

Both interventions consist of innovative new elements with an effective therapeutic background: BPT includes contents of physical activity and body experience, MMT the element of mental models with a long-term influence derived from research on decision making [30, 31]. As a significant number of patients still do not profit from existing psychotherapies [10], it seems sensible to develop different types of therapies and identify possible factors of influence in order to be able to personalize the therapeutic technique to enhance the benefits of this technique for all at a later stage of development.

During and after the intervention period, participants are free to begin or continue other therapeutic treatments offered by the German health care system without suffering any disadvantages. Previous ongoing treatment plans will not be changed by their participation in this study. Therapeutic treatment outside of the study will be assessed in the video interviews.

Participation in the BPT is accompanied by a slight risk of injuries; however, this level of risk does not exceed the risks of other physical activities. In a study on sport-climbing injuries, an average number of 0.2 injuries per 1000 h of climbing (which has higher risks of severe injuries than bouldering) occurred in a sample of about 2000 climbers [90]. In our study, bouldering time is limited to a maximum of 10 × 2 h per patient. Hence, severe injuries are not expected. Irrespective of their group allocation, all participants are provided with road and accident insurance while participating in the study. In our previous studies, no SAEs occurred in more than 4000 h of bouldering. Nevertheless, interim analyses of SAEs are being performed on a regular basis in both intervention groups. If any analyses show a cumulation of SAEs in one group, the respective intervention will be terminated.

All participants’ suicidality and capability of collusion are being assessed during the diagnostic screening interview and at all measurement points in the video interviews as part of the MADRS. During the therapy sessions, therapists follow good clinical practice in monitoring for suicide risk. In cases of acute risks, they will establish suicide risk management plans.

The strengths of the present study are the randomization, the mixed methods approach, the naturalistic design with very few exclusion criteria, and the longitudinal character of the study with a long follow-up period of 1 year after the end of treatment. The use of manualized treatments in a naturalistic setting will contribute to the high internal and external validity of the study. The inclusion and exclusion criteria are being assessed via diagnostic screening interviews in contrast to self-report assessments. Additionally, the severity of depressive symptomatology as the primary outcome is being collected by blinded interviewers, and the interrater reliability is being assessed. A methodological limitation might be a possible selection bias due to people choosing to participate because they are interested in the therapies. Therefore, group preference is being taken into account during randomization, and it will be possible to compare subgroups with respect to their group preference. Also, the selection of a specific therapy on the basis of interest in the intervention is naturalistic and will hence contribute to higher external validity. Another limitation is the fact that the psychotherapeutic interventions themselves cannot be blinded. Furthermore, the clinical heterogeneity of the sample could lead to a reduction in effect sizes but would also strengthen external validity. As participants are free to continue with or begin other individual treatments during the study, possible confounding effects due to simultaneous interventions cannot be ruled out. However, ongoing and new treatments as well as changes in treatment plans during the study will be assessed at all measurement points, and the data will be considered in the analyses.

## Data Availability

The research group intends to publish data generated from this study in high-impact peer-reviewed open-access journals. Data are stored on protected devices at the University Hospital Erlangen. Fully anonymized data will be available upon reasonable request after the publication of results. The trial registry will be updated if protocol modifications are made. Model consent forms in the German language were approved by the Ethics Committee and will be made accessible upon request along with the participant information materials.

## Abbreviations

BMI: Body mass index
BPT: Bouldering psychotherapy
BSA-F: Bewegungs- und Sportaktivität Fragebogen
CBT: Cognitive behavioral therapy
CG: Control group
CRT-3: Cognitive Reflection Test
DSM-V: Diagnostic and Statistical Manual of Mental Disorders, Fifth Edition
FEPiG: Fragebogen zum Erleben von therapeutischen Prozessen in der Gruppe
GAD-7: Generalized Anxiety Disorder Scale-7
IE-4: Internal External Locus of Control
IGs: Intervention groups
ITT: Intention to treat
MADRS: Montgomery and Asberg Depression Rating Scale
MMT: Mental model therapy
MSMQ: Multidimensional State Mindfulness Questionnaire
PP: Per protocol
SAEs: Severe adverse events
SMS-PA-12: State Mindfulness Scale for Physical Activity
SOC: Sense of Coherence Scale
SWE: Skala zur Allgemeinen Selbstwirksamkeit
